#### Behavioral changes

✓ Attitude, knowledge(Based on relevant questionnaire items).✓ Mean total caloric intake (kcal/day), percentage of carbohydrates in total caloric intake (%)✓ Mean carbohydrate intake (g/day)✓ Percentage of fat in total caloric intake (%)✓ Mean fat intake (g/day)✓ Percentage of protein in total caloric intake (%)✓ Mean protein intake (g/day)✓ Mean dietary fiber intake (g/day)✓ Mean salt intake (g/day)For the intervention group only, the above will be calculated from the data entered into the mobile application (Calo Mama Plus Ninsanpu Course®).✓ Number of steps✓ SleepData from the activity and sleep monitor will be used✓ Breastfeeding rate (at 1 and 6 months postpartum)

(Based on relevant questionnaire items)✓ Duration of breastfeeding (12 months postpartum)(Based on relevant questionnaire items)✓ Indicators of breastfeeding process, breastfeeding desires (at 1 month postpartum)(Based on relevant questionnaire items)

#### Use of IoT devices/mobile applications (*intervention group only)

✓ Rates of IoT device wearing, measurements (activity tracker, weight, and body composition monitor)✓ Mean logins per day to mobile applications, hours viewed per day✓ Meal image/content upload status✓ Breastfeeding video viewing status✓ Intervention program continuation rate

Dropping out of the intervention program is defined as follows: If measurement data are not registered for 2 weeks or longer, an investigator will contact the participant by e-mail or phone to remind them to register their data. If they cannot be contacted or do not register data, contact will be attempted again every 2 weeks. If the participant still cannot be contacted at 6 or 12 months postpartum, or if they do not register any data, they will be removed from the program.✓ AdherenceLow adherence is defined as bottom 20% use of the IoT devices (weight, number of steps, etc.), of opening the mobile applications or of inputting meals during a 2-week period at the beginning of the study and at 6 and 12 months postpartum.✓ User-friendliness of the devices(Based on relevant questionnaire items)✓ Desire to continue using the IoT devices after the trial ends

(Based on relevant questionnaire items).

### Sample size

Assuming a -2% weight change at 12 months postpartum compared to before pregnancy in the non-intervention group, the trial was designed to detect whether the IoT/mobile application intervention would result in a -5% weight change at 12 months postpartum. To conduct a two-sided test with a standard deviation of 8% and significance level of 5% at 80% power, 226 participants in both groups are needed. Assuming loss of approximately 20% of participants from exclusion or drop-out, the target number of registrations is set to 270 women.

There are 6,000 deliveries each year at the trial institutions. If 10% of the women are obese, the total number comes to 600 per year. As pregnant women at up to 30 weeks of gestation are eligible for registration, 250 pregnant women at up to 30 weeks of gestation who have already visited the outpatient maternity clinic for checkups and 250 pregnant women who newly visit during the 5-month registration period will be eligible. Hence, it is expected to be possible to register the target number of participants.

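### The registration target of 270 covers about 16% loss, not the stated 20%: 226 evaluable women would need 283 registrations

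*Protocol article*

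**What the plan says.** All the figures stand in one paragraph of the protocol article, under Sample size.

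- Control group: "Assuming a -2% weight change at 12 months postpartum compared to before pregnancy in the non-intervention group".
- Intervention group: the programme "would result in a -5% weight change at 12 months postpartum".
- Test: "To conduct a two-sided test with a standard deviation of 8% and significance level of 5% at 80% power".
- Evaluable number: "226 participants in both groups are needed".
- Allowance for loss and target: "Assuming loss of approximately 20% of participants from exclusion or drop-out, the target number of registrations is set to 270 women".

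The paragraph does not show how the target was obtained from the evaluable number, and the article does not state the allocation ratio.

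**The concern.** Women who are excluded or drop out are lost from those registered. A loss rate therefore applies to the registration target, and the target has to be the evaluable number divided by one minus the loss rate. Multiplying the evaluable number by one plus the loss rate is a common shortcut that always gives too few. The target of 270 looks like the result of that shortcut.

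What is at stake is the consistency of three printed figures: the evaluable number with its power, the loss rate and the target. Anyone interpreting a null result will read the paragraph as a claim of 80% power after 20% loss. The allowance is not a formality in this trial. It has to cover exclusions as well as drop-out, the Statistical methods section removes randomized women from the full analysis set on three grounds, and the primary outcome needs a home-scale weight at 12 months postpartum.

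**Working it through.** **Inputs, all from Sample size unless noted**

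- Difference: −2% against −5%, so 3 percentage points
- SD: 8%, so the standardized difference is 3/8 = 0.375
- Two-sided 5% test, 80% power
- Loss: 20%
- Registration target: 270
- Allocation: 1:1 (my assumption; not stated)

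**Step 1. Reproduce the 226.** By the normal approximation, n per group = 2 × [8 × (1.960 + 0.842) / 3]² = 111.6, so 112 per group and 224 in total. The t-test version (noncentral t) gives 112.6, so 113 per group and 226 in total. This matches the stated number exactly. It supports the 1:1 assumption and settles that 226 is the total of the two groups. If it were 226 in each group, power would be about 98%, which is not the stated design.

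**Step 2. Registrations needed for 226 after 20% loss.** 226 / (1 − 0.20) = 282.5, so 283. The target of 270 is 13 short.

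**Step 3. What 270 delivers at 20% loss.** 270 × 0.80 = 216, or 108 per group. That is 10 women fewer than 226.

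**Step 4. The loss that 270 does cover.** 1 − 226/270 = 44/270 = 16.3%.

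**Step 5. Where 270 may come from.** 226 × 1.20 = 271.2, close to 270. This is an inference, and the inconsistency in steps 2 to 4 does not depend on it.

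**Step 6. Size of the consequence.** Power of a two-sample t-test (standardized difference 0.375, two-sided 5%) with 270 registered:

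| Loss | Women remaining | Power |
|---|---|---|
| 15% | 229.5 | 80.7% |
| 16.3% | 226 | 80.1% |
| 18% | 221.4 | 79.3% |
| 20% | 216 | 78.3% |
| 25% | 202.5 | 75.7% |

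The normal approximation gives 78.7% at 20% loss. With 108 per group, the difference detectable at 80% power is 3.06 points instead of 3.0.

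**The case against.** The strongest reply is that this is too small to matter. The loss is an assumption and is given only as approximate. The margin added is 44 women, and 44/226 = 19.5%, so the wording could loosely describe the margin instead of the loss. The shortfall is also finer than the inputs: both expected changes and the SD are whole percentages, and an SD of about 7.8% instead of 8% would restore 80% power with 108 per group.

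A second reply concerns the analysis. The primary analysis is a mixed-effects model for repeated measures adjusted for pre-pregnancy weight, and home weights are also scheduled at 1 and 6 months postpartum. A woman lost after one of those weights may still contribute information, unless she is excluded from the full analysis set. The t-test power in step 6 counts her as contributing nothing.

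Most of this stands, and it limits how far the point goes. A reader might infer that the trial as sized fails to deliver 80% power. The document does not support that as an unconditional statement. If loss is about 16% or less, 270 gives 226 women and the stated power. At 20% the deficit is under 2 points, and the planned model may regain part of it, by an amount that cannot be computed from the article.

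The reply does not remove the inconsistency. The sentence speaks of participants lost, which is a share of those registered, and at its own central value 226 is not reached. The approximate wording also allows losses above 20%, where the gap widens. Nor is this a matter of detail left to a fuller document, since the conflicting figures are printed side by side.

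**Conclusion.** The point holds as a minor arithmetic inconsistency. The evaluable number of 226, a 20% loss and a target of 270 cannot all be true. At 20% loss the target would have to be 283. The target of 270 leaves 216 women and tolerates about 16% loss.

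The consequence is about 78% power instead of 80% at 20% loss. This figure rests on 1:1 allocation, independent observations and a simple two-sample t-test on women with a 12-month weight. Since the repeated-measures model may do somewhat better than that t-test, 78% is an approximate and probably cautious figure for the planned analysis. Nothing here calls the design, the enrolment target or the choice of analysis into question.

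**What to change.** Restate the sentence so that its figures agree. Either of two wordings would do:

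- 270 registrations allow for about 16% loss at 80% power.
- 270 registrations with 20% loss leave 216 evaluable women (108 per group), with power of about 78%.

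The choice depends on which loss rate the investigators still consider realistic. If it is 20%, the second wording is the accurate one. Adding how 270 was obtained from 226 would remove any doubt.

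The cost is one sentence and a slightly less favourable stated figure, either the tolerated loss or the power. No extra enrolment and no change to the analysis are needed.

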### Statistical methods

The full analysis set (FAS) will comprise the randomized participants, excluding those who meet any of the following conditions:Trial intervention not implementedEndpoints not measured at baseline and after the start of the interventionDid not meet the inclusion criteria after enrollment or randomizationThe per protocol set will comprise a subset of the FAS that will follow the trial protocol, excluding those who fail to meet any of the following conditions:Scale: Data obtained from at least two measurements at 1, 6, and 12 months postpartum (1 day)Fitbit: Measurements taken at both 6 and 12 months postpartum (7 days)Application meal entries: At least one entry during 2 weeks at 6 and 12 months postpartumObesity articles: Viewed 8 of the 10 articles

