### Blinding

According to the nature of the intervention, the participants and research coordinator at each site will not be blinded to the allocation. However, the physician at each site will be blinded to the allocation.

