### Intervention

The intervention will be initiated on the day consent is provided during pregnancy to 1 year postpartum. The IoT intervention for this trial is defined as (1) automatically generated advice based on data (weight, body composition, activity, sleep) measured using IoT devices and meal records and photographs recorded with a mobile application (Calo Mama Plus Pregnant woman Course®) and (2) provision of articles and videos related to obesity and pregnancy via a mobile application.

The following IoT devices will be distributed to all participants: body composition monitor and scale (HBF-227t, Omron Healthcare Inc., Tokyo) and fitness tracker (Fitbit Inspire®, Fitbit Inc., San Francisco, CA).

Participants in the intervention group will use a mobile application (Calo Mama Ninsanpu Plus®). The target weight 1 year postpartum has been set at 93% of the pre-pregnancy weight. Participants will monitor themselves daily to the extent possible using the IoT devices (weight and body composition monitor, activity, and sleep tracker) and by entering meal records and photographs into the mobile application.

The mobile application (Calo Mama Plus Ninsanpu Course®) has the following four functions: 

It automatically generates personalized advice based on conditions during and after pregnancy. Personalized advice is generated automatically based on data (weight, body composition, activity, and sleep) measured with the IoT devices and meal records and photographs recorded by the mobile application, alongside considering how far long in the pregnancy the participant is or the number of weeks postpartum.It provides articles based on the number of weeks of pregnancy or postpartum. The articles are delivered once or twice a week on themes that match the number of weeks of pregnancy or postpartum.It provides breastfeeding advice. After delivery, advice on breastfeeding is provided that reflects the breastfeeding status (number of times the participant recorded breastfeeding and amount of milk).It plots the body weight during pregnancy. Weight measurements during pregnancy are plotted on a graph and advice on weight changes based on the pre-pregnancy BMI is provided.

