In addition, episodes from "Hana-chan's best chance for pregnancy and postpartum weight loss," a manga comic that discusses pregnancy and obesity, are automatically sent to the mobile application. The story consists of 10 episodes, with episodes 1–7 sent during pregnancy and episodes 8–10 sent after delivery (Supplementary Table 1).

The mobile application for pregnancy will be used during pregnancy until delivery; afterward, the participants will switch to a postpartum application, with the intervention resuming at 6 weeks postpartum and continuing until 1 year postpartum.

Participants in the non-intervention group will undergo regular maternity checkups, receive health guidance (usually until 1 month postpartum), and be provided with medical care covered by health insurance as needed. In Japan, women usually undergo maternity checkups approximately 15 times roughly throughout 10 months of pregnancy. The IoT devices (weight and body composition monitor, activity, and sleep tracker) must be worn when the data are collected (start of the study and at 1, 6, 12, and 24 months postpartum). The articles provided to the intervention group will also be available on a website.

During the study period, the research coordinator at each site will ask the participants in the intervention group if there is any inconvenience in using the device and mobile application. In both groups, useful information on infants will be regularly sent by e-mail after delivery to prevent dropouts.

Figure 2 shows the study timeline for intervention and data collection.

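### The full analysis set excludes women whose trial intervention was not implemented, a post-allocation ground that can act on the intervention arm only and leaves the primary comparison open to bias

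*Protocol article*

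**What the plan says.** Statistical methods gives the starting population of the main set: "The full analysis set (FAS) will comprise the randomized participants". From these women it then takes several groups away, in these words: "excluding those who meet any of the following conditions:Trial intervention not implementedEndpoints not measured at baseline". Two further grounds follow the first: endpoints not measured at baseline and after the intervention began, and failure of the inclusion criteria. None of the three is limited to one arm. The per-protocol set is then defined as a subset of the FAS with conditions on scale and tracker measurements, meal entries and article views.

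Intervention: "The IoT intervention for this trial is defined as (1) automatically generated advice based on data" from the devices and the app, together with (2) articles and videos sent through the app. "Participants in the intervention group will use a mobile application". For controls: "Participants in the non-intervention group will undergo regular maternity checkups, receive health guidance", plus insured medical care as needed. The scale and tracker are not confined to one arm: "The following IoT devices will be distributed to all participants".

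Blinding: "the participants and research coordinator at each site will not be blinded to the allocation".

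Analysis of primary outcome specifies a mixed model for repeated measures and a two-sided comparison at 12 months postpartum. It does not say which analysis set is used.

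**The concern.** An analysis set meant to preserve the randomised comparison should not lose women from one arm for something that happens after allocation. Controls have no trial intervention to implement, so no control can be removed on a matching ground. The result would compare a selected intervention arm with an unselected control arm.

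If women who never start the app would also have had less favourable weight at 12 months, their removal makes the intervention look better even with no true effect. The estimate would then no longer be the effect of being assigned to the intervention. The per-protocol set cannot serve as a check, because it sits inside the FAS and carries the same exclusion.

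**Working it through.** **Step 1. Who can meet the condition.** By the plan's own definition, the intervention is advice and content delivered through the app, and the intervention group uses it. Controls get usual care. They also receive the devices and can read the articles on a website, but neither is the app-based intervention as defined. So the condition can act on the intervention arm only.

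**Step 2. Whether such women would have data.** All participants receive the scale, and Data collection requires all of them to weigh themselves at 1, 6, 12 and 24 months postpartum. A woman who never started the app can therefore still have a 12-month weight, which this condition would discard. A woman with no postpartum weight would leave under the second FAS condition anyway, so the first condition adds nothing for her.

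**Step 3. The planned figures.** Sample size assumes −2% in controls and −5% with the intervention, a difference of 3 points, with SD 8%, two-sided 5% and 80% power. Normal approximation: n per arm = 2 × (1.960 + 0.842)² × 8² / 3² = 111.6, so 112 per arm and 224 in total. The t-test version gives 225.2 in total, so 113 per arm and 226, which is the stated figure. Equal allocation is assumed, as no ratio is given.

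**Step 4. Size of the possible bias.** Let f be the share of non-starters among intervention women who supply a postpartum weight, and D the number of points by which their mean weight change is worse than that of starters. With no true effect, the full-arm mean is the starters' mean plus f × D. Dropping non-starters from that arm alone shifts the difference by f × D in favour of the intervention. The document gives neither f nor D, so both are assumptions. The standard error is 8 × √(1/113 + 1/(113(1 − f))), and the two-sided error is P(|Z + bias/SE| > 1.96).

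| f | D (points) | Bias f × D | Share of 3 points | SE | Two-sided error |
|---|---|---|---|---|---|
| 5% | 2 | 0.10 | 3% | 1.08 | 0.0510 |
| 10% | 3 | 0.30 | 10% | 1.09 | 0.0587 |
| 10% | 4 | 0.40 | 13% | 1.09 | 0.0655 |
| 15% | 4 | 0.60 | 20% | 1.11 | 0.0841 |

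This is exact for a simple difference in 12-month means and approximate for the planned mixed model.

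**Step 5. Overlap with the second condition.** If 10% of the arm never start, only half of these supply a weight, and every starter does (all assumed), then f = 0.05 / (0.05 + 0.90) = 5.3%. With D = 4 the bias is 0.21 points instead of 0.40.

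**Step 6. Cost of keeping non-starters.** If 3 points is the effect among starters and non-starters gain nothing, the whole-arm difference is 3 × (1 − f): 2.85 points at 5%, 2.70 at 10% and 2.40 at 20%. Power at 226 is then about 76%, 72% and 62%.

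**The case against.** A reader might infer that the condition, taken literally, removes every control. The document does not support that as the plan: Sample size, Analysis of primary outcome and Analysis of secondary outcomes all assume two groups. The per-protocol conditions likewise include app-specific items without naming an arm, so this is condensed drafting.

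A reader might also infer that the primary result is shown to be biased. It is not, for these reasons:

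- Non-implementation could mean that staff failed to set up the app, which need not relate to outcome. The document deals with poor use elsewhere, as programme drop-out and low adherence.
- The intervention starts on the day of consent and each day's allocation is settled before recruitment, so few women may fail to start.
- Postpartum weights come from the device through the smartphone application, so many women who never engage may have no weight and leave under the second condition.
- The share and deficit are assumed, and the low case is negligible.
- The primary analysis section names no set, and the full protocol or analysis plan may hold further analyses.

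Most of this stands and limits the size of the claim, but it does not remove it. A delivery-failure reading still acts on one arm only. Non-implementation is not defined, and the text does not say whether it covers a woman who never moves to the postpartum application at 6 weeks, so its scope could be settled after data are seen. Leaving never-treated participants out of an FAS is easiest to defend when starting cannot depend on the arm. Here allocation is open and only one arm has anything to start. The point concerns a rule that the article states, not detail left to another document.

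**Conclusion.** The concern holds as a stated rule that leaves the primary comparison open to bias, not as a demonstrated bias. The condition can in practice act on the intervention arm only, after an open allocation, and neither defined set is an all-randomised comparison. That the FAS is the primary set is an inference, though the natural one, and the per-protocol set inherits the same exclusion.

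The direction probably favours the intervention, provided non-starters would have had worse weight outcomes. The size is unknown. The assumed range of 0.1 to 0.6 points is 3% to 20% of the planned 3-point effect, with a two-sided error of about 5.1% to 8.4% instead of 5%. The bias is nil if non-starting is unrelated to outcome, or if no non-starter supplies a postpartum weight.

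**What to change.** - Delete the first FAS condition, on non-implementation of the intervention.
- Analyse all randomised women in the arm allocated, whether or not the app was started. Exclude only for eligibility failures that rest on facts fixed before allocation and are applied identically in both arms, or for lack of any postpartum weight for the repeated-measures model.
- Name this FAS as the set for the primary analysis.
- Keep having started the intervention as a per-protocol condition only.

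This is a short change of wording and needs no new data, because both arms already have scales and a scheduled 12-month weight. The cost is that non-starters dilute the estimated effect: slightly if they are few, and with the loss of power shown in the working if they are more common. The estimate then reflects the effect of assignment. The change should be made before outcome data are seen by arm.

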All participants will measure their blood pressure at home over 3 days at 6, 12, and 24 months postpartum. The HBF-227t sphygmomanometer manufactured by OMRON Healthcare Co. will be used. Measurements will be taken twice a day in the morning (within 1 h of waking up, after urinating, before taking any medication, and after resting for 1–2 min) and before going to sleep (after resting in the sitting position for 1–2 min). In principle, two measurements will be taken each time.

Table 1 shows the schedule for the trial.

**Table 1 Tab1:** Study timeline for intervention and data collection

		Trial duration								
		Obtain consent		Intervention						Completion
Pregnancy, postpartum			Start of trial	During pregnancy	Delivery	1 month postpartum	6 weeks postpartum	6 months postpartum	12 months postpartum	24 months postpartum
	Obtain consent	×								
	Registration	×								
Regular management	Regular medical care, guidance (maternity checkups)Regular health guidance			○ (maternity checkup→→		○ (1-month postpartum checkup)				
Measure at home	Weight, body composition		○			○		○	○	○
	Activity, sleep		○					○	○	○
Blood pressure	Blood Pressure							○	○	○
Postal checkups	Postal checkup (blood glucose, HbA1c, etc.)							○	○	○
App intervention	Weight, activity, sleep		●	→→→→→→→			●→→→	→→→→→→	→	
	Meal photos		●	→→→→→→→			●→→→	→→→→→→	→	
Mother and Child Handbook	Maternity checkup data (urine test, blood pressure, weight)					○				
	Pregnancy outcome data					○				
Questionnaire	Background, lifestyle		○							
	EPDS		○			○				
	Breastfeeding status					○		○	○	
	Breastfeeding process					○				
	Behavioral changes (attitude, knowledge)		○					○	○	
	User-friendliness of devices							○	○	
	Desire to continue using IoT after end of study								●	

○ Both groups, ● intervention group only

If there are missing data, the research coordinator at each site and trial secretariat will contact the participants. Data from the weight and body composition monitor, activity and sleep tracker, and online questionnaires will be stored on the Internet server. The data file will be secured with a password, and access to information will be limited to designated members such as the researchers and the trial secretariat. Paper-based documents such as consent forms will be stored at each site.

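### The per-protocol set, as written, requires app meal entries that controls have no means to make, so it holds no controls and cannot support a between-group comparison

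*Protocol article*

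**What the plan says.** Under Statistical methods, the Protocol article forms one per-protocol set as a subset of the full analysis set (FAS), "excluding those who fail to meet any of the following conditions". Four conditions follow:

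- "Scale: Data obtained from at least two measurements at 1, 6, and 12 months postpartum (1 day"
- "Fitbit: Measurements taken at both 6 and 12 months postpartum (7 days"
- "Application meal entries: At least one entry during 2 weeks at 6 and 12 months"
- for the obesity articles, "Viewed 8 of the 10 articles"

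None of the four is limited to an arm.

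Elsewhere the article places meal logging in one arm. The Intervention section says "Participants in the intervention group will use a mobile application" and describes self-monitoring there "by entering meal records and photographs into the mobile application". In Table 1 (Data collection) the meal-photo row carries only the filled symbol, and the key reads "Both groups, ● intervention group only". Behavioral changes computes dietary intake from the app for the intervention arm alone, and meal uploads are an intervention-only outcome under Use of IoT devices/mobile applications. Controls receive the scale, the tracker, usual care and website access to the articles (Intervention).

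**The concern.** A per-protocol set for a two-arm comparison has to be one that members of both arms can enter. Here one entry condition is a component of the experimental treatment, and the other arm is not given it. Applied literally, the rule removes the whole control group.

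A pre-specified set that cannot be formed will have to be redefined later, possibly once outcomes are visible. The obvious repair, applying the app conditions to the intervention arm only, brings a second problem. Intervention women would then be kept for sustained app use while controls face no matching requirement. If women who keep logging and reading also tend to lose more weight whatever their allocation, the arms differ even when the intervention does nothing.

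**Working it through.** **1. The plan's own figures.** Sample size gives -2% against -5% (a difference of 3 points), SD 8%, two-sided 5%, power 80% and 226 participants in total. The normal approximation gives n per arm = 2 × (1.960 + 0.842)² × (8/3)² = 111.6, so 112 per arm and 224 in total. The exact t-test solution is 112.6, so 113 per arm and 226 in total. The stated figure reproduces, with 1:1 allocation assumed. The sample size is not in dispute; it supplies the 3 points and the SD of 8% used below.

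**2. Each condition against what each arm is given.**

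| Condition | Intervention | Control |
|---|---|---|
| Scale, at least two measurements | can meet | can meet (device given to all) |
| Tracker at 6 and 12 months | can meet | can meet (device given to all) |
| App meal entries at 6 and 12 months | can meet | cannot meet (no meal-entry app) |
| 8 of 10 articles viewed | can meet | possible through the website, but no recording of their viewing is described |

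The conditions apply jointly, so one impossible condition is enough. The number of controls in the set is 0, and neither the between-group difference nor its standard error can be estimated. This rests on the meal-entry condition alone.

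**3. If the app conditions applied to the intervention arm only.** Let a fraction p of that arm be retained on engagement, and let engagement correlate r with percentage weight change (r is given as a magnitude, with more engaged women losing more). Under normality and no true effect:

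shift = E[Z | top p] × r × SD, where E[Z | top p] = φ(z)/p and z is the cut-off leaving a fraction p above it.

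E[Z | top 50%] = 0.798 and E[Z | top 80%] = 0.350. SD = 8% is from Sample size; p and r are assumptions, because the article gives neither.

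| Retained p | r = 0.1 | r = 0.3 |
|---|---|---|
| 50% | 0.798 × 0.1 × 8 = 0.64 | 0.798 × 0.3 × 8 = 1.92 |
| 80% | 0.350 × 0.1 × 8 = 0.28 | 0.350 × 0.3 × 8 = 0.84 |

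The range is about 0.3 to 1.9 points, or 9% to 64% of the planned 3 points (0.28/3 and 1.92/3). The formula takes controls as unselected. They would in fact be screened on scale and tracker data too, which would offset part of the shift.

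**4. The scale condition and the endpoint.** On its natural reading it asks for two of three time points. A woman with weights at 1 and 6 months but none at 12 could therefore enter the set, although the primary outcome is weight change to 12 months.

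**The case against.** The strongest reply is that the set is introduced as those who follow the trial protocol, and the protocol never asks controls to log meals. On that view the app conditions are plainly meant for the intervention arm, and the wording is merely loose. This is probably the intent, but the text does not say so. The definition is stated in full rather than left to another document, and the one-sided selection in step 3 would remain.

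The exclusion clause could also be read as dropping only those who meet none of the conditions. Controls with scale or tracker data would then stay in. So would intervention women who never logged a meal or opened an article, which defeats the purpose of the set; it is not the natural reading.

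Several limits on the point do stand:

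- A reader might infer that the trial's main result is compromised. The article does not support that. The per-protocol set is defined once, and none of the primary, secondary or subgroup analysis sections assigns an analysis to it.
- A reader might infer that controls fail the article condition as well, because viewing is tracked in the app. No section says how article viewing is recorded, and controls have website access.
- The meal condition is a low bar (one entry in two weeks), so it need not isolate the most engaged users. The article condition is stricter.
- The tracker condition is open to both arms, and steps and sleep are secondary outcomes. There is no need to remove it.

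**Conclusion.** The point holds for the set definition. As written, the per-protocol set contains 0 controls and can give no between-group result. That follows from the article's own text and needs no numerical assumption.

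Severity is moderate. An FAS-based primary estimate is unaffected, and no stated analysis depends on the set.

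The 0.3 to 1.9 points apply only if the app conditions are confined to the intervention arm. They illustrate what assumed retention and correlation would imply, before any offset from screening both arms, and do not estimate the bias in this trial. It would be tempting to quote only the upper end, about two thirds of the planned effect, but the article contains nothing that singles out that scenario.

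**What to change.** Define the between-group per-protocol set by conditions either arm can meet: eligible, no crossover to the other arm's treatment, no discontinuation as the protocol already defines it, and weight measured at 12 months for the primary endpoint. Take the meal-entry and article conditions out of this set and report app use descriptively within the intervention arm, where the plan already summarises logins, uploads and adherence. The tracker condition may stay.

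If the sponsor prefers to keep app conditions, state which arm each one applies to and label the resulting comparison supportive only. A complier-average analysis with allocation as instrument is optional. A threshold version would be doubtful, because women below an app-use cut-off still receive advice and articles.

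The cost is a small wording change, best made before outcome data are seen. The downside is that the per-protocol set would no longer reflect app adherence.
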